##### Secondary endpoints

Sternal bone healing grade at the end of the trial evaluated by computed tomography using a 6-point scale according to Gregory S. Stacy [20], evaluation made by a certified radiologist (evaluation time point: 6th month).Total number of intensive care unit (ICU) days spent with mechanical ventilation during the original (first) heart surgery hospitalization, obtained from patient records in the hospital information system (evaluation time point: hospitalization discharge).Total number of ICU days during the original (first) heart surgery hospitalization, obtained from the hospital information system (evaluation time point: hospitalization discharge).Number of hospital readmissions for sternotomy complications within the clinical trial duration obtained from patient records in the hospital information system (evaluation time point: 6th month).Total number of treatment days for pericardial and/or pleural effusions during the original (first) heart surgery hospitalization and/or re-hospitalizations, obtained from patient records in the hospital information system.

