### Trial design {8}

This clinical trial is conducted as a monocentric, randomized, double-blind, placebo-controlled trial, with the goal to enroll 600 patients over 4 years: approximately 300 subjects in the placebo arm and 300 in the treatment arm. Males and females aged 18 to 95 years who fulfill the indication criteria for undergoing cardiac surgery with sternotomy may be included in this clinical trial, if they meet the eligibility criteria (as shown in Table 2).

**Table 2 Tab2:** Patient eligibility criteria

Inclusion criteria	Exclusion criteria
Patient:	Patient:
• Undergoing cardiac surgery with sternotomy	• With known hyperparathyroidism
• With baseline calcium, phosphate, and alkaline phosphatase values in physiological ranges	• Treated or supplemented by vitamin D or its derivatives (alfacalcifediol, calcitriol, paricalcitol) including ergocalciferol (vitamin D2) when used regularly for 3 months before entering the trial
• With sufficient ability to understand and cooperate in planned medical examinations	• Undergoing repeated sternotomy
• Czech or Slovak speaker with permanent residence and citizenship in the Czech Republic	• With chronic renal insufficiency associated with osteodystrophy (hyperphosphatemia, hypocalcemia)
• With initial calcidiol levels less than 75 nmol/L	• With severe hepatic impairment associated with cirrhosis, Child-Pugh score B and C
• With signed informed consent to enter the trial	• With known metabolic bone disease
• Male or female between 18 and 95 years of age	• With cancer associated with primary or secondary risk of bone damage
	• With known immunodeficiency
	• With short bowel syndrome or other malabsorption syndrome that limits absorption of lipophilic vitamins
	• With long-term cardioactive glycoside and/or thiazide diuretic treatment that cannot be replaced with alternative treatment during cardiac surgery hospitalization
	• Prior to the planned radiotherapy affecting the body skeleton
	• With known allergic reaction or intolerance to IMP
	• With long-term teriparatide treatment or other parathyroid hormone
	• With long-term bile acid sequestrant treatment which cannot be replaced by any other treatment during cardiac surgery hospitalization
	• With long-term corticosteroid treatment or other immunosuppressive drugs
	• With another medical condition which the investigator considers a risk for the patient during the trial

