## Methods: participants, interventions, and outcomes

### Study setting {9}

The trial is monocentric, based at the Cardiac Surgery Department of Na Homolce Hospital, Prague, Czech Republic.

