### Criteria for discontinuing or modifying allocated interventions {11b}

No interventions or drug dose changes will be made during the trial. If there is any problem related to the clinical trial, patient participation in clinical trial will be terminated. The decision for termination can be made from both sides:
Patient decisionA trial participant may leave the trial at any time without providing a reason.Examiner decisionDue to the fact that the clinical trial is based on the administration of cholecalciferol or placebo, termination of the clinical trial by the investigator is very unlikely. Nevertheless, in rare circumstances described below, the examiner may decide to exclude a subject from the trial due to preventive reasons.

Criteria for the clinical trial discontinuing by examiner:
Cholecalciferol intoleranceHypercalcemia—serum total calcium concentration higher than 2.75 mmol/L, measured in at least one of the scheduled laboratory testsHyperphosphatemia—concentration of total phosphorus in the serum above 1.61 mmol/L, measured in at least two of the scheduled laboratory testsAn increased serum alkaline phosphatase activity two times higher than the physiological range, measured in at least two of the scheduled laboratory testsA high level of calcidiol above 200 nmol/L, measured in a targeted manner in case of suspected overdose at any time during CTThe need to use prohibited medicationPregnancy

Interruption or termination of CT for other reasons is always subject to the judgment of the examiner (medical doctor), but due to its design is not expected.

In both decisions of this participant’s termination, trial subject will be asked to do the following:
To return the rest of the IMP at the hospital Cardiac Surgery DepartmentTo be medically examined within 14 days from the medication withdrawal (calcidiol concentration, calcium concentration)—these examinations can also be requested by a general practitioner in the place of trial subject residence

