#### Assessments and visits

Daily visits to the participants will be conducted by a cardiac surgeon while in the hospital for whole period of hospitalization to evaluate relevant outcome measures. The cardiac surgeon will examine the sternotomy for possible complications. All the biochemical examinations are indicated by any medical doctor in the cardiac surgery ward (anesthesiology specialist, cardiology specialist, or cardiac surgeon). The last evaluation will be done on the day of discharge, then after in the sixth week and in the sixth month after cardiac surgery (including sternotomy).

Participant timeline is displayed in Table 4.

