### Plans to promote participant retention and complete follow-up {18b}

There are no extra plans to promote participant retention. Trial participants have no financial reward for participating in the clinical trial. Automatic SMS reminders for trial medication and all medical appointments are introduced. Patients will return completed patient questionnaires (confirming all medication administrations) at the end of the clinical trial. Complete follow-up will be made by the clinical trial coordinator by telephone.

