### Methods in analysis to handle protocol non-adherence and any statistical methods to handle missing data {20c}

Any missing data will be explained. Multiple imputations of missing outcome data will be used for sensitivity analyses.

If there are missing data regarding to primary endpoints, the trial participant will be excluded from the final trial evaluation.

If there are missing data from the secondary outcomes, the isolated missing value will be not used for the final trial evaluation.

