### Adverse event reporting and harms {22}

Adverse events are reported in the database and reported to the Czech Institute for Drug Control (SUKL).

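### The only source named for readmissions and for effusion days during re-hospitalization is the hospital information system, so an admission to another hospital may go uncounted without being flagged as missing

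*Protocol article*

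**What the plan says.** Protocol article, Secondary endpoints: the readmission outcome is the "Number of hospital readmissions for sternotomy complications within the clinical trial duration obtained from patient records in the hospital information system", evaluated at month 6. Treatment days for pericardial or pleural effusion, which cover the first stay and any re-hospitalization, are also taken from patient records in that system. The ICU-day and ventilation-day endpoints use the same system but are confined to the first stay.

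Study setting {9}: "The trial is monocentric, based at the Cardiac Surgery Department of Na Homolce Hospital, Prague, Czech Republic". Trial design {8}, Table 2, sets the catchment: "Czech or Slovak speaker with permanent residence and citizenship in the Czech Republic".

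Three other routes of information appear elsewhere in the article:
- Assessments and visits: after discharge, patients are examined "then after in the sixth week and in the sixth month after cardiac surgery".
- Plans to promote participant retention {18b}: "Complete follow-up will be made by the clinical trial coordinator by telephone".
- Safety outcomes and Adverse event reporting {22}: hospitalization is a listed type of serious adverse event, and adverse events go into the trial database.

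For missing secondary data, section {20c} says that "the isolated missing value will be not used for the final trial evaluation".

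**The concern.** A hospital's own information system is a complete source for anything that happens during the index stay. It need not be complete for events after discharge, when a patient who lives far from Prague may be admitted closer to home. The protocol carries the same source over from the in-stay endpoints to two endpoints that run past discharge.

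The particular difficulty is that the loss would leave no trace. The readmission endpoint is a count, so a patient whose only readmission took place elsewhere appears as a valid zero. Nothing marks the value as missing, so neither the exclusion rule for missing secondary values nor a sensitivity analysis by multiple imputation would act on it.

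Readmission for a sternotomy complication should be uncommon, so a few lost events matter. At stake are an understated readmission rate, a smaller absolute difference between arms and lower power. A further awkwardness is possible: the same outside admission could be tabulated as a serious adverse event and yet be absent from the readmission endpoint, with no reconciliation described.

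**Working it through.** **Step 1. The plan's own figures.** The article gives no readmission rate, expected event count or power for this endpoint, so there is no stated figure to reproduce. The nearest is the sample size for the primary endpoint in section {14}: complication rates of 5% and 1%, α = 0.05, β = 0.2, 284 per arm. The two-sided pooled formula is

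n = [z₀.₉₇₅·√(2·p̄·(1−p̄)) + z₀.₈₀·√(p₁(1−p₁) + p₂(1−p₂))]² / (p₁−p₂)²

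With p₁ = 0.05, p₂ = 0.01 and p̄ = 0.03:

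[1.960·√0.0582 + 0.842·√0.0574]² / 0.0016 ≈ 284.3, or 285 rounded up.

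The 284 therefore reproduces as a two-sided calculation. (The text calls it one-sided; that is a separate matter.) It is used here only to show that 5% and 1% are the working complication rates. Readmission rates may well differ from them.

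**Step 2. What each possible source covers.**

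| Source in the article | Could it show an outside admission? | Tied to the two endpoints? |
|---|---|---|
| Hospital information system | Only if it was reported back and filed | Yes, the one named source |
| Visits at week 6 and month 6 | Yes, if asked | No |
| Coordinator's telephone contact | Yes, if asked | No |
| Serious adverse event hospitalizations | Yes, if reported | No |

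**Step 3. Effect of equal under-capture.** Let c be the share of true readmissions that reach the records, the same in both arms. Observed rates are c·p₁ and c·p₂. The ratio p₂/p₁ is unchanged; the absolute difference becomes c·(p₁−p₂).

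**Step 4. Illustration A.** Assumptions, not from the documents: 4% versus 1% of patients with any readmission. With 300 per arm, power is the exact binomial probability that the two-sided Pearson chi-square test rejects at 0.05. Expected events are 300·c·0.04 and 300·c·0.01.

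| Capture c | Expected events | Difference (points) | Power |
|---|---|---|---|
| 100% | 12.0 vs 3.0 | 3.00 | 69.1% |
| 95% | 11.4 vs 2.85 | 2.85 | 66.6% |
| 90% | 10.8 vs 2.7 | 2.70 | 64.0% |
| 80% | 9.6 vs 2.4 | 2.40 | 58.0% |
| 60% | 7.2 vs 1.8 | 1.80 | 44.1% |
| 50% | 6.0 vs 1.5 | 1.50 | 37.1% |

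**Step 5. Illustration B.** Assumption: each complication at the section {14} rates leads to one readmission, so 5% versus 1%, or 15 versus 3 expected events (18 in all). The same exact method gives 86.4% at full capture, 77.4% at 80% and 53.6% at 50%.

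Section {20a} plans a two-group t test for secondary endpoints. If each patient is scored 0 or 1, that is in practice the same comparison at this sample size, so the figures serve for it too.

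**The case against.** The best case against the point has five parts.

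*The wording.* A reader might infer that readmissions elsewhere are by rule excluded and scored as none. The article does not say so. It contains no restriction to that source alone and no zero-scoring rule. Records at the trial hospital may include history taken, or outside reports filed, at the week 6 and month 6 visits, and the endpoint is evaluated at month 6. This stands. What remains is that the zero follows from the one named source whenever an outside admission is not reported back.

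*The other routes.* The visits, the telephone contact and serious adverse event reporting could all bring an outside admission to light. This also stands, so a loss is possible rather than established. It does not remove the point, because none of these routes is stated to feed the two endpoints.

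*Care near home.* A reader might take the discontinuation section as evidence that complications would be treated locally, since it says that "these examinations can also be requested by a general practitioner in the place of trial subject residence". That clause concerns calcidiol and calcium tests after a participant leaves the trial. It says nothing about where a sternal complication would be admitted, and the point does not rest on it. Nationwide eligibility makes outside admission plausible; no section shows that it happens.

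*Size.* The readmission rates and the capture shares are assumed. If 95% of readmissions are captured, power in illustration A falls only from 69% to 67%. Even with full capture the endpoint is not well powered there, and the trial was not sized on it.

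*Condensation.* The full protocol may describe how outside discharge reports are obtained. That would excuse silence. Here, however, the article does state a source, and that source is narrow for an outcome that runs past discharge.

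**Conclusion.** The point holds as a modest one. The only source stated for readmissions, and for effusion days during re-hospitalization, does not by itself cover admissions to other hospitals. The trial has one centre and a national catchment, and an unreported outside admission would pass as a genuine zero that the missing-data rule cannot see.

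The size cannot be determined from the documents. Under the assumed 4% versus 1%, power falls from 69% to between 67% and 58% if 5% to 20% of readmissions are missed, and to 37% if half are missed. These figures assume equal capture in both arms, which is reasonable under blinding but is not guaranteed by anything written.

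A reader might go further and infer bias in favour of one arm, or damage to the main result. The documents support neither. Similar loss in both arms leaves the rate ratio unchanged while shrinking the absolute difference. The primary endpoint is assessed by clinical examination and does not use this source, so it and its sample size are unaffected.

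**What to change.** In Secondary endpoints, define both outcomes as admissions to any hospital within the trial period. State the sources as the hospital information system plus direct questioning at the week 6 visit, the month 6 visit and the coordinator's telephone contact. Add that these are reconciled with hospitalizations recorded as serious adverse events and confirmed by the outside discharge report where one is available. Record for each patient whether the question was asked, so that a true zero can be told apart from an unknown and section {20c} can then apply to the unknowns.

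The cost is one or two extra questions at contacts already planned, and an occasional request for an outside report. Visits, sample size and the primary analysis do not change.

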#### Safety outcomes

Safety endpoints related to impaired biochemical examinations, calculated incidence in two parallel patient groups with cholecalciferol or placebo treatment:
Serum calcium concentration out of physiological range (values within the range 2.05–2.9 mmol/L considered physiological)Alkaline phosphatase activity out of physiological range (values within the range 0.66–2.2 μcat/L considered physiological)Serum phosphate concentration out of physiological range (values within the range 0.65–1.61 mmol/L considered physiological)Endpoints related to non-serious adverse effects, calculated incidence in two parallel patient groups with cholecalciferol or placebo treatment:
ConstipationLoss of appetiteNauseaOther non-serious adverse effectEndpoints related to serious adverse events, calculated incidence in two parallel patient groups with cholecalciferol or placebo treatment:
DeathLife-threateningHospitalization (initial or prolonged)Disability or permanent damageRequired intervention to prevent permanent impairment or damage (devices)Important medical event

Efficacy and safety endpoint evaluation timetable is shown in Table 3.

**Table 3 Tab3:** Efficacy and safety endpoint evaluation timetable

Week	Examination of the subject by the investigator	Laboratory examination of the subject	Evaluation of subject’s quality of life	Imaging examination of the subject
**0**	**Initial interview with the patient + initial medical examination + decision to offer clinical trial participation to the patient**	**Initial complete biochemical examination including monitored parameters (calcium, phosphate, calcidiol, and ALP)**	**Acquaintance with the trial + provision of signed informed consent**	
**1**		**Continuous determination of several biochemical parameters during hospitalization: serum calcium (minimally every other day), ALP values (minimally once during hospitalization), and serum phosphate (minimally once during hospitalization)**		
**2**	**Examination of the surgical wound before hospital discharge**	**Laboratory tests before discharge**		
**6**	**Continuous examination of surgical wound**	**Continuous evaluation of serum calcium, ALP, and phosphate**		
**26**	**Exit examination of the surgical wound**	**(1) Final lab. test of serum calcium, ALP, and phosphate; (2) calcidiol level; (3) doctor’s entry in Questionnaire No. 1**	**Final evaluation of quality of life according to Questionnaire No. 2**	**Computed tomography of the chest**

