## Introduction

### Background and rationale {6a}

Vitamin D3 (cholecalciferol) is produced by the human skin from its precursor 7-dehydrocholesterol, or received from diet. Initially, cholecalciferol undergoes 25-alpha hydroxylation in the liver, forming calcidiol. Another hydroxylation takes place primarily in the kidneys, where calcidiol is metabolized to calcitriol by 25-hydroxyvitamin D3-1α-hydroxylase. The crucial physiological effect is to increase serum calcium levels by stimulating renal calcium retention, intestinal calcium resorption, and bone resorption to maintain normocalcemia. Calcitriol predominantly affects bone, tooth, and cartilage mineralization indirectly by regulation of local calcium and phosphate levels; however, there is also direct action on mineralization as calcitriol has genomic and non-genomic effects on cells of mineralizing tissues [1]. Calcitriol binds to the vitamin D nuclear receptor (VDR). VDRs, present in many tissues, are involved in the expression of more than 500 of the total 20,488 genes in the human genome [2]. The 25-OH hydroxyvitamin D (calcidiol) with its elimination halftime of 15 days is the best indicator of the vitamin D saturation state in the body, as it takes into account both vitamin D3 produced endogenously in the skin and exogenous vitamin D2 and D3 from the diet. The definition of individual vitamin D saturation status based on blood calcidiol concentration is controversial [3]. For the purposes of our clinical trial, we have defined it as displayed in Table 1, with a value for serum calcidiol of 80 nmol/L as the low end of the optimal range. Serum calcidiol below this level results in impaired calcium absorption and carries a risk of bone loss and osteoporotic fractures [4, 5].

**Table 1 Tab1:** Definition of vitamin D saturation status based on serum calcidiol levels

Serum calcidiol concentration in ng/mL and nmol/L, respectively		Vitamin D saturation status—interpretation of values
< 10 ng/mL	< 24 nmol/L	Deficiency
10–20 ng/mL	25–49 nmol/L	Insufficiency
20–30 ng/mL	50–74 nmol/L	Sufficiency
30–50 ng/mL	75–125 nmol/L	Optimal level (considered for this clinical trial)
> 100 ng/mL	250 nmol/L	Risk of toxicity

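### The calcium safety endpoint counts low and high values as one event, so it can dilute or cancel an excess of high calcium, and its upper limit conflicts with the termination criterion

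*Protocol article*

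**What the plan says.** **Endpoint.** The protocol article, Safety outcomes, gives the calcium endpoint as "Serum calcium concentration out of physiological range", and counts 2.05–2.9 mmol/L as physiological. The measure for this group of endpoints is stated as "Safety endpoints related to impaired biochemical examinations, calculated incidence in two parallel patient groups with cholecalciferol or placebo treatment". Phosphate and ALP are defined in the same either-direction way.

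**Expected direction.** Background and rationale {6a} says of the vitamin: "The crucial physiological effect is to increase serum calcium levels".

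**Termination criteria.** The sections on discontinuing interventions {11b} and on interim analyses {21b} list four laboratory criteria: calcium above 2.75 mmol/L, phosphorus above 1.61 mmol/L, ALP above twice its range, and calcidiol above 200 nmol/L. All four are high values. One calcium value is enough, whereas phosphorus and ALP each need two.

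**Timing.** The safety section refers to a timetable: "Efficacy and safety endpoint evaluation timetable is shown in Table 3". During the hospital stay that table has "serum calcium (minimally every other day"). At week 6 it has "Continuous evaluation of serum calcium, ALP, and phosphate", and at week 26 "Final lab. test of serum calcium, ALP, and phosphate". The article does not say whether incidence is counted per patient over the whole trial, per period or per visit.

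**Test.** The section on statistical methods {20a} names a chi-square test for the primary endpoint and a t test for secondary endpoints. It names no test for safety endpoints.

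**The concern.** The endpoint looks in both directions, while the foreseeable laboratory risk lies in one. Two things can then happen to a true excess of high calcium in the cholecalciferol arm.

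- **Dilution.** Low values that occur equally in both arms add events that carry no information about the product. The contrast shrinks in relative terms and its noise grows.
- **Offset.** If the product raises calcium, it may also prevent some low values. Fewer low events in the treated arm then subtract from the extra high events in the same count.

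Either way, the report could read as no difference in calcium abnormalities when the arms differ in the direction that matters.

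A second problem lies in the same definition. The endpoint's upper limit is 2.9 mmol/L, but the termination criterion calls calcium hypercalcaemia above 2.75 mmol/L. A patient can meet that criterion at, say, 2.80 mmol/L and have no event on the calcium endpoint.

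**Working it through.** The document states no expected rate or power for this endpoint, so there is no figure of its own to reproduce. What follows is an illustration.

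**Inputs from the protocol article**
- About 300 patients per arm (Sample size {14}).
- Significance level 0.05 (Statistical methods {20a}).
- In-range calcium at entry (Table 2), so out-of-range values arise after entry.

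**Inputs that are assumptions**
- Above-range calcium (h) in 5% of treated and 1% of placebo patients.
- A background rate q of other out-of-range values, equal in both arms and independent of h.
- A two-sided Pearson chi-square test, with exact binomial power.

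**Step 1, dilution.** The pooled rate in an arm is 1 − (1 − q)(1 − h). For q = 10%: placebo 1 − 0.90 × 0.99 = 10.9%; treated 1 − 0.90 × 0.95 = 14.5%.

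| Background q | Placebo | Treated | Risk ratio | Power |
|---|---|---|---|---|
| 0% (high values alone) | 1.0% | 5.0% | 5.0 | 86% |
| 5% | 5.95% | 9.75% | 1.64 | 41% |
| 10% | 10.9% | 14.5% | 1.33 | 26% |
| 20% | 20.8% | 24.0% | 1.15 | 16% |
| 40% | 40.6% | 43.0% | 1.06 | 9% |

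A normal approximation gives 82% in place of 86% for high values alone, and 41%, 26% and 15% at backgrounds of 5%, 10% and 20%. The pattern does not depend on the method.

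**Step 2, other assumed excesses (normal approximation).** For 3% v 0.5%, power is 65% alone and 21%, 14% and 9% at backgrounds of 5%, 10% and 20%. For 6% v 2%, it is 71% alone and 38%, 25% and 15%.

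**Step 3, offset.** Suppose low calcium occurs in 10% of placebo patients and 6% of treated patients, with high calcium at 1% and 5% as before. Placebo: 1 − 0.90 × 0.99 = 10.9%. Treated: 1 − 0.94 × 0.95 = 10.7%. A fivefold excess of high calcium leaves no visible difference.

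**Step 4, the two upper limits side by side.**

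| Analyte | Termination criterion {11b}, {21b} | Upper end of endpoint range (Safety outcomes) |
|---|---|---|
| Phosphate | above 1.61 mmol/L | 1.61 mmol/L |
| Calcium | above 2.75 mmol/L | 2.9 mmol/L |

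The phosphate limits agree. The calcium limits leave a band above 2.75 and up to 2.9 mmol/L that is hypercalcaemia in one place and in range in the other.

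**Step 5, sampling over time.** With an assumed stay of 7, 10 or 14 days, sampling every other day gives at least 4, 5 or 7 hospital values. Taking one value each at weeks 6 and 26 (the number at week 6 is not stated), hospital values are 4/6 = 67%, 5/7 = 71% or 7/9 = 78% of the total. This matters only if incidence is counted over all samples, which the article does not say.

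**The case against.** **The rates are invented and no safety test is planned.** This stands as a limit on the figures. The documents give no rate of low or high calcium, and the power values describe a test that the article does not name. The change in the reported rates does not need a test, however: in Step 3 the two incidences come out nearly equal whatever is done with them.

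**There are other routes to see harm.** This also stands. The termination criterion looks only at high calcium and has the lower limit, so an excess could show as terminations. The section on prohibited medication ties some co-medication to regular calcium monitoring, and adverse events are reported to the regulator. A reader might infer that the pooled comparison is the main safeguard, since there is no data monitoring committee. The documents do not support that. Still, termination is at the examiner's discretion, and the article describes no comparison of terminations between arms.

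**High calcium is not named as the main harm.** Correct. A reader might infer it from the single-value rule, but the section on interim analyses {21b} presupposes no harmful effect and the criteria are not ranked. The point needs only the stated direction of effect and the direction of the termination criteria.

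**Pooling over time is not in the text.** Correct. A reader might infer from Table 3 that any sample at any time counts, and so that the early hospital days dominate. The article sets no counting rule, and an analysis plan that is not shown may split by period. It would also be wrong to say that little product has been given early on, because a 25,000 IU bolus precedes surgery. Timing therefore supports only an optional addition. The either-direction definition is different, because the article itself fixes it.

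**Conclusion.** The point holds in this form. The calcium endpoint as written merges two opposite abnormalities and so can dilute or cancel an excess of high calcium. How much is lost depends on how often low calcium occurs, which the documents do not give. It ranges from nothing at zero background to a fall from about 86% to 41%, 26% or 16% power at backgrounds of 5%, 10% or 20%, for an assumed 5% v 1% and a two-sided chi-square test at 300 per arm. These figures show that the endpoint can mask harm, not that it will.

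The conflict between 2.75 and 2.9 mmol/L rests on no assumption. The passages contradict each other, and as they stand some values that meet the termination criterion are not endpoint events. Both parts deserve correction. Neither affects the primary efficacy analysis.

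**What to change.** 1. In Safety outcomes, report above-range and below-range incidence as separate rows by arm for calcium, and do the same for phosphate and ALP.
2. Have the sponsor reconcile the upper calcium values in Safety outcomes and in the sections on discontinuing interventions {11b} and interim analyses {21b}, so that the above-range row and the termination criterion agree. Which value should apply is for the sponsor to decide. This has to come before the new row is tabulated, because splitting the endpoint alone would still leave the band between the two limits uncounted.
3. Optionally, tabulate the hospital stay separately from weeks 6 and 26, and state how incidence is counted over time. The reason is strongest for calcium; phosphate and ALP need be measured only once in hospital.

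The cost is a few extra table rows from data already collected, and one clarification of the text. No new samples or visits are needed.
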